## Abstract

**Background:**

Skin-to-skin care immediately following delivery is a common practice for term infants and has been shown to improve cardiorespiratory stability, facilitate early bonding, and promote breastfeeding. Since 2007, the use of skin-to-skin care has been practiced for preterm infants from 32 weeks of gestation in the delivery room at St. Olav’s University Hospital. In the present study we aim to investigate whether skin-to-skin care following delivery is safe, and how it affects early and late outcomes compared to standard care for very preterm infants.

**Methods/Design:**

A randomized controlled trial (RCT) of skin-to-skin care in the delivery room for very preterm infants born at gestational age 28^0^–31^6^ weeks with birth weight >1000 grams. Infants with severe congenital malformations or need of intubation in the delivery room are excluded. A detailed checklist and a flowchart were prepared for the study, and all involved professionals (neonatologists, neonatal nurses, obstetricians, anesthesiologists, midwives) participated in medical simulation training prior to study start on February 1, 2014. A consultant in neonatology and a neonatal nurse are present at all deliveries. Infants with birth weight <1500 grams receive an intravenous line with glucose, amino acids, and caffeine citrate in the delivery room. Infants with gestational age <30 weeks are routinely put on continuous positive airway pressure (CPAP). After initial stabilization, infants are randomized to skin-to-skin care or are transferred to the nursery in an incubator. Primary outcome is cognitive development at 2 years measured with the Bayley Scales of Infant Development, Third Edition. Secondary outcomes are safety defined as hypothermia, respiratory failure, and/or cardiopulmonary resuscitation, physiological stability after birth and motor, language and cognitive development at 1 year for the child, and mental health measured with the State-Trait Anxiety Inventory (STAI) at discharge, and at 3 months and 2 years after expected date of delivery for the mothers.

**Discussion:**

The study may have important implications for the initial care for very preterm infants after delivery and increase our understanding of how early skin-to-skin care affects preterm infants and their mothers.

**Trial registration:**

ClinicalTrials, NCT02024854. Registered on 19 December 2013.

**Electronic supplementary material:**

The online version of this article (doi:10.1186/s13063-016-1730-5) contains supplementary material, which is available to authorized users.

## Background

Worldwide, 15 million infants are born preterm annually [1], and preterm birth is one of the largest direct causes of neonatal mortality and morbidity [2]. Compared to full-term infants, preterm infants are at increased risk of neurodevelopmental impairments [3–5]. This also includes lower self-esteem, social relations, and quality of life in adulthood [6]. There is growing evidence that mental and behavioral problems in children born preterm last into adulthood [7–13]. These societal and medical consequences of preterm births have led to a growing interest in developmental care models to optimize neurodevelopmental outcomes. Different approaches aiming to support infants and parents have been established in neonatal intensive care units (NICUs) in recent years, and some of these early intervention programs seem to have a positive effect on long-term function up to preschool age [5, 14, 15]. The first hours after birth represent a sensitive period for the very low birthweight infant (VLBW), and mothers who see their infant within 3 hours after birth are likely to establish a more secure attachment to the infant compared to those who do not see their infant within 3 hours [16]. Parents are increasingly acknowledged as primary caregivers for their preterm-born infant; despite the need for intensive care, most NICUs try to facilitate early parent-infant bonding. Education of parents to understand subtle signs and signals from their tiny, preterm-born infants is considered an investment in an optimal home environment for the child. From being forced to separate from their newborn infant due to restrictions of visiting hours in NICUs, parents are now generally encouraged to stay with their infant as much as possible [17, 18].

Kangaroo care (KC) [19], family-centered care (FCC) [20], Newborn Individualized Development Care and Assessment Program (NIDCAP) [21, 22], and a variety of early intervention programs emphasize the importance of establishing early parent-infant interaction to support an optimal development [23–25]. Facilitating early skin-to-skin care (SSC) is one way of supporting early parent-infant bonding and is also associated with improved physiological stability [26, 27] and decreased cortisol reactivity [28]. In addition, a recent World Health Organization (WHO) guideline on interventions to improve outcomes for preterm infants, strongly recommends early SSC as thermal care for preterm infants weighing <2000 grams [29].

Skin-to-skin care in the delivery room (DR) has been studied for preterm infants from 32 weeks of gestation [30]. However, to the best of our knowledge, SSC in the DR and the operating room (OR) has not been systematically investigated for infants born at gestational age (GA) <32 weeks. Obvious obstacles to do so would be the need for medical equipment and competent personnel, usually available only in the NICU. Breathing support, need of surfactant, intravenous access, and monitoring equipment are needed in a large proportion of infants below 32 weeks. To combine medical interventions with early SSC, a trained team and formalized guidelines are required to ensure the medical safety of the infant. Specific challenges arise with early SSC in the OR after cesarean section (C-section).

Moving treatment and medical procedures from the NICU into the DR and OR requires cooperation across specialties and departments. Pediatricians and neonatal nurses have to work outside their familiar NICU environment, while gynecologists, midwives, anesthesiologists, nurse specialists in anesthesia, and operating room nurses have to adjust their work and procedures to the presence of the preterm infant on the mother’s chest.

In the present study we aim to investigate whether SSC following delivery is safe, and how it affects early and late outcomes compared to standard care for preterm infants born at GA 28^0^–31^6^ weeks.

The purpose of this article is to present the study design and a description of the intervention, as well as provide a detailed outline of how the intervention was planned and implemented in a multidisciplinary team. Schedule of enrolment, interventions, and assessment are outlined in Table 1.

**Table 1 Tab1:** Schedule of enrolment, interventions, and assessment

Activity/assessment	Staff member	Approximate time to complete	Before delivery	t_0_	t_1_	t_2_	t_3_	t_4_	t_5_	t_6_	t_7_	t_8_	t_9_	t_10_	t_11_	t_12_	t_13_	t_14_
Informed consent	Neonatal nurse/physician	15 minutes	x															
Inclusion/exclusion form	Neonatal nurse	5 minutes		x														
Randomization sealed envelopes	Neonatal nurse	1 minute			x													
Heart rate	Neonatal nurse	30 sec				x	x	x	x	x								
Respiration rate	Neonatal nurse	30 sec				x	x	x	x	x								
Oxygen saturation	Neonatal nurse	30 sec				x	x	x	x	x								
Body temperature	Neonatal nurse	30 sec				x	x	x	x			x	x					
Blood glucose	Neonatal nurse	5 minutes						x^1^	x^1^		x			x				

### Aims

#### Primary aim

To study the effect of early SSC versus standard care (SC) for very preterm infants (28^0^–31^6^ weeks) on cognitive scores at 2 years corrected age, measured with the Bayley Scales of Infant Development, Third Edition (Bayley-III).

#### Secondary aims

To assess safety of the intervention by measuring incidence of hypothermia (temperature <36 °C) or respiratory failure during the first 2 hours of life.To estimate the effect of the intervention on complications to prematurity (intraventricular hemorrhage (IVH) or periventricular leukomalacia (PVL), seizures, necrotizing enterocolitis (NEC), treatment for persistent ductus arteriosus (PDA), and bronchopulmonary dysplasia (BPD)).To estimate the effect of the intervention on physiological stability during the first 24 hours.To estimate the effect of the intervention on maternal mental health at discharge from the NICU and when the child’s corrected age is 3 months and again at the corrected age of 2 years by using the State-Trait Anxiety Inventory (STAI).To investigate if the intervention affects the fidgety type of general movements and detailed aspects of the early motor repertoire at the corrected age of 3 months, using the General Movement Assessment (GMA) and the Assessment of Motor Repertoire – 2 to 5 months (AMR).To estimate the effect of the intervention on neurodevelopmental outcomes including cognition, language, and motor function at the corrected age of 1 year, and language and motor function at the corrected age of 2 years assessed with Bayley-III.To investigate the effect of the intervention on social and emotional competence at the corrected age of 3 months and at 2 years with the Ages & Stages Questionnaire - Social-Emotional

## Methods/Design

### Project context

The study is currently being carried out at St. Olav’s University Hospital in Trondheim. Trondheim is the third largest city in Norway, and St. Olav’s Hospital serves a population of almost 446,000 and is a tertiary care center for preterm infants <30 weeks of gestation. Approximately 50 infants with GA <32 weeks are born every year at St. Olav’s Hospital.

The NICU at St. Olav’s Hospital has 21 beds, with seven beds for intensive care, seven intermediate, and seven in a step-down unit. Altogether, there are 107 nurses (many part-time) and six consultants working in the NICU. The maternity ward has two sections with seven delivery rooms each and about 120 midwives employed.

Delivery rooms are in the same building as the NICU, but on separate floors (fifth and second floor, respectively). The operating room and the postoperative ward are in the same building and at the same floor as the NICU.

### Study design

The study is designed as an RCT with randomization to skin-to-skin care (SSC) or standard care (SC) in an incubator after delivery.

### Study population

Singleton and twin preterm infants with GA 28^0^–31^6^ and a BW >1000 grams in a stable medical condition delivered either vaginally or by C-section are candidates for inclusion. Twins are randomized to the same intervention. Infants with severe malformations not compatible with life, or requiring surgery within hours to days after birth (e.g. esophageal atresia, abdominal wall defects or neural tube defects), will be excluded.

Infants who need intubation and mechanical ventilation, or CPAP with more than 40% oxygen to maintain a saturation above 90% at 10 minutes of age, are excluded. Mothers have to be awake (not under general anesthesia) during C-section.

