#### Sample size and statistical analyses

Primary analysis: sample size calculations are performed for a two-sample *t* test for comparing the Bayley Scale of Infant and Toddler Development, Third Edition, cognitive scale between the intervention (SSC) and control (SC) groups at 2 years of corrected age. To obtain a power of 80% for detecting a difference of 7.5 in mean score, using SD = 15 and significance level α = 0.05, 64 preterm infants are needed in each group. To allow for withdrawals, the sample size is set to 68 in each group.

Secondary analysis: differences between the SSC and SC groups for continuous variables will be analyzed using two-sample *t* tests, or Mann-Whitney *U* tests for data with non-normal distributions. Categorical variables will be analyzed by the Pearson chi-square test or Fisher’s exact test. *P* values <0.05 are considered statistically significant. Due consideration of multiple testing will be made when interpreting the results. All data will be presented and analyzed in accordance with the updated CONSORT guidelines for randomized trials [39].

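### Twin pairs are randomised as a unit, but the sample size and the named tests treat every infant as independent

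*Protocol article*

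**What the plan says.** Under Study population, the protocol article admits "Singleton and twin preterm infants with GA" in the stated range and adds: "Twins are randomized to the same intervention".

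Under Sample size and statistical analyses, the primary analysis paragraph says that "sample size calculations are performed for a two-sample" t test on the Bayley-III cognitive scale at 2 years corrected age. The inputs are given as "To obtain a power of 80% for detecting a difference of 7.5 in mean score", "using SD = 15 and significance level α = 0.05". The result is "64 preterm infants are needed in each group. To allow for withdrawals, the sample size is set to 68 in each group".

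For the secondary analysis, "differences between the SSC and SC groups for continuous variables will be analyzed using two-sample" t tests, or Mann-Whitney U tests if the data are not normal. Categorical outcomes get the Pearson chi-square or Fisher's exact test. The article mentions no design effect, within-pair correlation, expected twin share, mixed model, GEE or cluster-robust error. Its only caveat on the analysis concerns multiple testing.

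**The concern.** A pair allocated together is a cluster of two. Twins share a pregnancy, a home and genes, so a positive correlation between their cognitive scores is the reasonable expectation. Two infants from one pair then carry less information about the treatment difference than two unrelated infants.

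The article's allocation rule therefore does not match its sample size or its list of tests. What is at stake depends on the analysis used. A test that ignores pairs understates the standard error and rejects a true null hypothesis too often. A test that respects pairs keeps its 5% level but has less power than the article states.

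**Working it through.** **Inputs from the article:** difference 7.5, SD 15, alpha 0.05, power 80%, 64 evaluable and 68 recruited infants per group. Sidedness is not stated; two-sided reproduces the figure.

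**Step 1: reproduce the plan's figure.** The standardised difference is 7.5/15 = 0.5. For independent infants the exact t calculation gives 63.8 per group, hence 64. Power is 80.1% at 64 and 82.5% at 68. The stated number is right for independent infants, and at 64 there is no spare power.

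**Step 2: allow for pairs.** Let f be the share of infants in complete enrolled twin pairs and ICC the within-pair correlation. Neither is in the article, so both are assumptions.

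- Design effect, all infants weighted equally: DE = 1 + f × ICC; effective n = 64/DE.
- Efficient weighting (mixed model): effective n = 64 × [(1 − f) + f/(1 + ICC)].
- Type I error of the plain t test: 2 × [1 − Φ(1.96/√DE)].

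Central case, f = 0.3 and ICC = 0.5: DE = 1 + 0.3 × 0.5 = 1.15; effective n = 64/1.15 = 55.7. With efficient weighting, 64 × (0.7 + 0.3/1.5) = 57.6.

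| f | ICC | DE | Valid power, 64 per group | Same, efficient model | Valid power, 68 per group, no losses | Type I error, plain t test |
|---|---|---|---|---|---|---|
| 0.1 | 0.3 | 1.03 | 79.0% | 79.2% | 81.4% | 5.3% |
| 0.2 | 0.3 | 1.06 | 77.8% | 78.2% | 80.2% | 5.7% |
| 0.3 | 0.5 | 1.15 | 74.4% | 75.8% | 76.9% | 6.8% |
| 0.4 | 0.8 | 1.32 | 68.3% | 71.9% | 71.0% | 8.8% |

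The 68-per-group column uses equal weighting.

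**Step 3: does the margin for withdrawals cover it?** 68/64 = 1.0625. The four extra infants per group absorb a design effect of about 1.06, and only if nobody is lost by 2 years.

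**Step 4: check by simulation** (40,000 replicates, plain t test, 64 per group).

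| f | ICC | Type I error | Rejection rate at a 7.5-point difference |
|---|---|---|---|
| 0.2 | 0.3 | 5.6% | 79.7% |
| 0.3 | 0.5 | 6.7% | 78.3% |
| 0.4 | 0.8 | 8.8% | 77.0% |

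The plain test stays near 80% only because its true alpha is above 5%. This is why the two consequences have to be kept apart.

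**The case against.** The strongest reply is that this is a condensed article. It ties the t test to the primary outcome only through the sample size calculation, and the sentence on how data will be analysed belongs to the secondary analysis. A full protocol or SAP may specify a clustered model. That is fair. A reader might infer that the primary p-value and confidence interval will certainly be anti-conservative; the article supports this only if the t test it names is the one used. The sample size does not benefit from the same defence. A clustered analysis would correct the p-values but could not restore the stated power at 64.

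The size is also open to challenge. Each twin must meet the eligibility criteria, so some pairs may contribute one infant and form no cluster. With a 10% share the loss at 64 is about 1 to 3 points. This stands, and is why the range starts there.

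Some stronger readings are tempting but not supported:

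- *Inflated type I error and lost power occur together.* They belong to different analyses, as the simulation shows.
- *The maternal anxiety outcome (STAI) counts twin mothers twice.* The outcomes section has the mothers completing the questionnaire, and nothing indicates one record per infant.
- *The figures above carry over to the safety and other infant outcomes.* The same mismatch exists there, but the correlations may differ and none is given.
- *Covariate adjustment would win back most of the lost power.* The article gives no figure for the variance that covariates would explain.

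**Conclusion.** The point holds. The article's pair-wise allocation of twins is inconsistent with a sample size in independent infants and with a list of tests that all assume independence. The direction follows from the text once pairs are enrolled and their scores are positively correlated. The size does not, because twin share and ICC are not given.

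Over the assumed 10% to 40% share and ICC of 0.3 to 0.8, either valid power at 64 per group is about 79% to 68% (79% to 72% with an efficient mixed model; 74% to 76% in the central case), or an unadjusted t test runs at about 5.3% to 8.8% instead of 5%. The loss is modest in most of this range, but it touches the primary test and the only power statement in the article.

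**What to change.** Name an analysis that accounts for the mother for the primary and all other infant-level outcomes. This can be a linear mixed model with a random mother effect, or GEE or cluster-robust standard errors by mother with a small-sample correction. Use the logistic or GEE analogue for binary outcomes.

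Restate the power at 64 and at 68 per group over a stated range of twin share and ICC. Recruitment was still open, with 27 infants included up to June 2016. The article does not say how many were twins, but the sponsor's own records should, and that can inform the range.

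If the sponsor prefers to keep 80%, multiply 64 by 1 + f × ICC before the allowance for withdrawals. In the central case this is 64 × 1.15 = 73.6, so 74 evaluable per group, or 74 × 68/64 = 78.6, so 79 with the same allowance. An efficient mixed model would need 64/0.9 = 71.1, so 72 evaluable.

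Restating power at the present size costs a slightly less favourable figure and a little more analysis work. It changes nothing in how the trial is run.

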### Intervention

For all infants of eligible women, cord milking is advised immediately following delivery and before the infant is placed on the resuscitation unit. Predefined blood samples are taken from the umbilical cord. Blood gas is taken from the umbilical artery before cord clamping, while blood for hemoglobin, leukocytes, thrombocytes, C-reactive protein (CRP) and blood typing is sampled after the cord clamping.

After the initial stabilization, the infant is treated and evaluated according to checkpoint 1 on the checklist, and eligibility is decided by the consultant (Fig. 1). Infants randomized to standard care are transferred to the NICU in an incubator after stabilization. The father will usually follow the newborn to the NICU, while the mother will come as soon as possible after delivery.

**Fig. 1 Fig1:**
[figure not shown]
Flowchart illustrating the first 2 hours after birth

All infants with a BW <1500 g, irrespective of randomization, are given parenteral nutrition (glucose and amino acids) after the initial stabilization. Infants with a GA <30 weeks receive CPAP, infants ≥30 weeks get CPAP if clinically indicated. If necessary, surfactant can be administered via a thin catheter in the trachea during spontaneous breathing on CPAP (“surfactant without intubation” (SWI) if oxygen requirement exceeds 35% on CPAP and/or the infant has signs of moderate to severe respiratory distress. After the infant is stabilized in skin-to-skin position on the mother’s chest (SSC) or in a closed incubator and transferred to the NICU (SC), the infant is evaluated again (checkpoint 2) according to the checklist (Fig. 1).

Infants in the intervention group are offered SSC up to 2 hours after delivery – in the delivery room after vaginal delivery, or in the recovery room after C-section. A consultant and a neonatal nurse are responsible for the infant, while a midwife takes care of the mother. After C-section, the same personnel from the NICU and from the maternity ward are present in addition to specialist nurses from the postoperative ward. When the infant is stabilized on the mother’s chest, the consultant can leave the DR or postoperative ward in agreement with the neonatal nurse in charge. The consultant is nearby and easily reachable by telephone.

Further treatment during the hospitalization does not differ between groups. According to the unit’s guidelines, both mothers and fathers have unrestricted access to the NICU and are encouraged to have as much skin-to-skin contact with their preterm infant as possible.

### Simulation-based training (SBT)

Simulation-based training (SBT) is effective for medical education [31], facilitates multidisciplinary training [32], and can be tailored to individual needs with no risk for human patients. Before study start, simulation-based training was facilitated for five consultants, fifteen neonatal nurses and ten midwives. One gynecologist, one anesthesiologist, and one operating nurse were observers during one SBT. The SBT was a collaboration with the Medical Simulation Center (MSC) at St. Olav’s University Hospital/NTNU. The instructors from the MSC (one pediatrician and one specialist nurse) had formal European standard instructor training. An in situ scenario, reflecting the complexity of the admittance of a very preterm infant, was customized and conducted in the OR and DR during a total of seven training days.

Prior to the SBT at St. Olav’s Hospital, the teams were informed about the equipment, the environment, and the procedures for the initial stabilization and the intervention. Each trainee participated actively in one or two scenarios per training day. Immediately before the scenario, each team received a case history with information about GA and birth weight, saturation level, heart rate, and the work of breathing. Any change in physiological parameters was visible on a monitor, and the team had to act based on the infant’s condition. Each team comprised two neonatal nurses, a consultant in neonatology, and one or two midwives. One person outside the resource team acted as a mother in labor during all training days.

### Outcomes measures

#### Primary outcome

##### Bayley Scales of Infant and Toddler Development, Third Edition (Bayley-III)

The Bayley-III is a screening test that includes assessment of cognition, language (receptive and expressive), and motor function (gross and fine) in infants and young children from 0 to 42 months and provides a measurable and validated cognitive quotient [33]. The occupational therapist conducting the Bayley for ages 1 and 2 years are unaware of the intervention group.

